**Potential Benefits of the Proposed Research to Human Subjects and Others**

Participants may find that responding to questions about depressive symptoms and suicidal ideation increases their awareness of these experiences, or that monitoring makes them feel more connected to or cared for by the research staff, which would promote improved mental health. Additionally, as we will continually monitor risk for suicide throughout the study and contact participants for risk assessments as necessary, participants may be protected against risk of suicidal behavior. Finally, our experience with adolescents participating in similar research is that they often enjoy the opportunity to interact with field staff, to engage in an interesting self-study, and to feel as if they are making a contribution to research on the lives of other teenagers. There will be no cost to participants.

**Potential Benefits to Society**

Information developed from this study may help researchers in the future. The expected scientific yield of the project is substantial. There is much to be learned from the project. Findings have the potential to have measurable implications on policy, prevention, and treatment efforts. The greatest benefit will be to future cohorts of adolescents who will benefit from what is learned from this research project.

The risks associated with this study are minimal and reasonable, particularly in light of the fact that significant knowledge will be gained.

1. **Statistical Analysis**

**Data preparation.** Six negative affect measures will be defined via composite averages and individual scores using EMA items: 1) the average over 5 items assessing depleted mood (scores for feeling Sad, Self-hatred, Numb, Hopeless, and Fatigued), 2) the average over 2 items assessing negative cognitive impacts (scores for feeling Disinterested and Inattentive), 3) the average over 3 items assessing negative activation (scores for feeling Agitated, Irritated, and Anxious), 4) the average over 3 items assessing passive suicidal ideation (scores for Thoughts about death, Wishing suffering could be over, and Better off as dead), 5) the individual item for suicidal urges, and 6) the individual item for non-suicidal self-injury urges. All items will be measured on a 0 (No, not at all) – 100 (Yes, very much) scale. Acute cannabis use will be defined as a binary indicator variable (1 = self-reported use in the hour preceding the current random prompt, 0 = no use in the last hour).Additionally, whether cannabis was used in the last hour to improve negative mood will be assessed on a 0 (No cannabis use) and 1 (No, not at all) – 100 (Yes, very much) scale.

**Statistical models.** Separate analyses will be conducted for each negative affect measure. Statistical models will assume that a) data are a mixture of a non-zero continuous component and zeros, and b) the continuous component will follow a beta distribution (i.e., scores will be scaled to be between 0 and 1). Models will include 1) a participant-varying lag-1 autocorrelation term (to handle repeated measures) and 2) a participant-varying probability term governing the occurrence of zeros (to allow for individual differences). Additional covariates will include weekday (categorical, Monday-Sunday), time of day (categorical, 6:00-11:00, 11:00-16:00, 16:00-21:00), age (continuous), and gender (categorical). To test specific hypotheses, additional predictors will be included as needed for a) the beta regression, b) the residual variance term of the beta regression, and c) the probability term governing zeros.

**Data analysis.**

**Aim 1: To test if negative mood and SI are temporarily relieved and stabilized through acute cannabis use (i.e., negative reinforcement cycle).** We will only use phase 1 data, the 2-week baseline period in which all participants may use cannabis. *Hypothesis 1.1:* We hypothesize that negative affect measures for a) the current random prompt, and b) the prior random prompt (a lag-1 term) will predict 1) greater cannabis use independent of motivating reason (i.e., lower probability for the zero component of the model), and 2) higher scores for motivated cannabis use to improve negative mood. Negative affect measures will therefore be converted to z-scores for this analysis and included as predictors for both the zero and non-zero components of the model. *Hypothesis 1.2:* We hypothesize that the binary indicator for cannabis use in the last hour will predict lower, less variable scores for the negative affect measures. Therefore, the binary use indicator will be included as a predictor for the beta regression residual variance term as well. *Hypothesis 1.3 (exploratory):* There will be within-subject correlates (e.g., concurrent other substance use, social context of use) and between-subject factors (e.g., cannabis use and depression severity, history of suicidal behavior) that moderate relationships between acute cannabis use and negative affect.

**Aim 2: To test if negative mood and SI initially increase with the start of abstinence and then decrease in both mean levels and variability after cannabis wash-out.** We will use phase 1 – 3 data, including predictors for a) group differences (CB-Abst vs. CB-Mon), b) differences by phase (phase 3 vs. phase 1 and phase 2 vs. phase 1), and c) terms for the group by phase interactions. All terms will be included as predictors for the beta regression residual variance term as well. We will only include data for the CB-Abst group with confirmed abstinence for phases 2 – 3. *Hypothesis 2.1:* We hypothesize that CB-Abst will show higher mean negative affect scores and greater variability during phase 2 compared to phase 1, while CB-Mon will show no differences between phases. *Hypothesis 2.2:* We hypothesize that CB-Abst will show lower mean negative affect scores and less variability during phase 3 compared to phase 1, while CB-Mon will show no differences between phases.

**Exploratory analyses:** To further assess heterogeneity in suicidal ideation, we will conduct a set of

exploratory analyses for hypotheses 1.1 – 2.2 looking at all 5 individual items for suicidal ideation. To examine the impact of participants who are versus are not receiving mental health treatment, we will conduct a set of exploratory analyses for hypothesis 1.1 – 2.2 including a binary indicator for receipt of mental health treatment as an additional covariate. Additionally, we will conduct exploratory analyses for sleep and circadian rhythms. Sleep, circadian, and physical activity exploratory Fitbit metrics include: *Sleep duration*: mean and standard deviation [StD]) over the main sleep period, the day, and 24hrs; short (<6 hrs) and long (>9hrs) mean nocturnal sleep duration; *Sleep fragmentation*: Mean and StD of 7-day sleep efficiency and wake after sleep onset; *Sleep timing placement*: Mean sleep onset, offset, and mid-point; categorized also as advanced (sleep onset <0900) and delayed (sleep onset >0200); *Sleep timing variability:* Across-day StD of sleep onset, inter-and intra-day stability; sleep offset, and sleep mid-point; relative activity- adjusted amplitude (Roberts et al., 2020); *Physical activity:* Overall activity, time spent walking, in moderate and physical activity. Timing of maximal physical activity will be used in analyses of rest-activity rhythm. Data will be processed in a customized data management environment that interfaces with Fitbit cloud servers. This platform provides secure data acquisition and management tools that facilitate remote data collection without the need to return devices for data extraction. Using an in-house algorithm that captures continuous heart rate sensor data at 1-5-sec intervals, we will calculate minutes of non-wear time (i.e., absence of a pulse for ≥60 secs), enabling us to determine compliance and distinguish between real and spurious sedentary time. Missing data will be handled using interpolation. Labeled sleep stage data will be retrieved at a granularity of 30s, activity counts at 60s, and the heart rate at 1s. Sleep-wake metrics will be generated using signals from accelerometry, heart rate, and heart rate variability processed by Fitbit’s proprietary, validated algorithm (Dillon et al., 2005). Valid sleep data will be defined as non-nap sleep durations >3 hr. Physical activity will be derived from daily step counts detected by Fitbit’s triaxial accelerometer, which agrees with direct observation, and will be reported as daily and intraday (per minute) step counts. Using step counts, we will calculate minutes spent doing sedentary, light, moderate, and vigorous activity. Metrics will be calculated for each 24-hour period, generating averages and within subject standard deviations (to assess within-subject variability).

**Multiple testing.** We will use the false recovery rate adjustment to control for multiple testing across the 6 negative affect measures separately for each hypothesis (Benjamini, 1995).

*Sleep & Circadian Rhythms (Exploratory).* Fitbits will be worn throughout the trial to assess changes in sleep. Sleep, circadian, and physical activity exploratory Fitbit metrics include: *Sleep duration*: mean and standard deviation [StD]) over the main sleep period, the day, and 24hrs; short (<6 hrs) and long (>9hrs) mean nocturnal sleep duration; *Sleep fragmentation*: Mean and StD of 7-day sleep efficiency and wake after sleep onset; *Sleep timing placement*: Mean sleep onset, offset, and mid-point; categorized also as advanced (sleep onset <0900) and delayed (sleep onset >0200); *Sleep timing variability:* Across-day StD of sleep onset, inter-and intra-day stability; sleep offset, and sleep mid-point; relative activity- adjusted amplitude;192 *Physical activity:* Overall activity, time spent walking, in moderate and physical activity. Timing of maximal physical activity will be used in analyses of rest-activity rhythm.

**Missing Data***.* Some data will inevitably be missing. We will explore patterns of missingness to determine if missingness is occurring at random (MAR) (i.e., unrelated to the value of the missing observation) or missing not at random (MNAR). For each analysis, we will use a variety of recommended strategies to address the issue of missing data (e.g., multiple imputation, maximum likelihood estimation) (Schafer & Graham, 2002). Consistency in findings across missing data methods will enhance our confidence in the findings. If findings are discrepant, we will assume that participants randomized to CB-Abst have resumed using cannabis, if they are lost to follow-up.

**Protocol non-adherence.** Analyses involving phase 1 and/or phase 2 of EMA data collection, will only consider CB-Abst participants who have biochemically-validated CB abstinence for two months because the goal is to study the effect of abstinence on change in mood and SI. If fewer than expected CB-Abst abstain from CB use for the full two months, we will form Helmert contrasts: those in CB-Mon (a), CB-Abst who do not abstain (b), and CB-Abst who abstain (c). The 1^st^ Helmert contrast will compare a to b+c and will be the intent to treat comparison. The 2^nd^ contrast will compare b to c, which corresponds to the post hoc sensitivity analysis of interest. Similar considerations will be made if participants in CB-Mon incidentally discontinue CB use during the study.

**Power analysis and justification of recruitment targets for the confirmatory cohort.** The R package ‘EMAtools’ (version 0.1.3; Kleiman, 2017) was used to determine the power for the proposed analyses. Preliminary analyses from the exploratory study found effect size estimates for significant effects ranged from 0.19 to 0.44, and that 77% of participants completed all phases of the study, completing on average 76% of all prompts. Estimates of the power were therefore computed to detect a weak effect (a Cohen’s d of .2) based on linear multi-level models using the nesting structure for the proposed EMA analyses and an intra-class correlation of .09. Table 1 shows the breakdown of estimates power based on the hypothesis being tested under two scenarios: 1) an ideal scenario with the full proposed number of participants and responses, and 2) a realistic scenario where 77% of participants complete 76% of entries.

Table 1: Power estimates by hypothesis and attrition scenario (ideal versus worse-case)

| Hypothesis | N (%) for sample size | N (%) of completed entries | Power |
| --- | --- | --- | --- |
| 1.1 - 1.2 | 200 (100%) | 112 (100%) | 99% |
|  | 154 (77%) | 85 (76%) | 93% |
| 2.1 - 2.2 | 200 (100%) | 224 (100%) | 99% |
|  | 154 (77%) | 170 (76%) | 94% |

1. **Monitoring and Quality Assurance**

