SI are temporarily relieved and stabilized through acute cannabis use (i.e., negative reinforcement).

*Hypothesis 1.1:* Negative mood will predict subsequent same-day cannabis use events as well as greater self-reported motivation to use cannabis for mood improvement (EMA Phase 1; Baseline as Usual).

*Hypothesis 1.2:* Negative mood and SI reported within one hour following cannabis use will be lower in intensity and less variable than mood and SI reported during same-day random-prompt EMA reports occurring ≥1 hours since last cannabis use (EMA Phase 1; Baseline as Usual).

*Hypothesis 1.3 (exploratory):* There will be within-subject correlates (e.g., concurrent other substance use, social context of use) and between-subject factors (e.g., cannabis use and depression severity, history of suicidal behavior) that moderate relationships between acute cannabis use and mood and SI.

**Aim 2:** To test if negative mood and SI decrease in overall (mean) levels and variability after cannabis

wash-out.

*Hypothesis 2.1:* Among CB-Abst but not CB-Mon, negative mood and SI reported during random prompt EMA reports will intensify and become more variable throughout the first week of sustained cannabis withdrawal (EMA Phase 2; Randomized Withdrawal) compared to random, non-use events during baseline cannabis use as usual (EMA Phase 1; Baseline as Usual).

*Hypothesis 2.2:* Negative mood and SI reported during EMA random prompts after 8 weeks of abstinence (EMA Phase 3; Randomized Sustained Abstinence) will be lower in intensity and variability than negative mood and SI reported during EMA random prompts occurring during random, non-use events during baseline cannabis use as usual (EMA Phase 1; Baseline as Usual) and withdrawal (EMA phase 2; Randomized Withdrawal). There will be no difference in mood or SI intensity or variability across the 3 EMA phases in CB-Mon.

1. **General Description of Study Design**

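### Hypothesis 1.1 uses mood at the current prompt to predict cannabis use in the hour before that prompt, so this predictor has the wrong time order and can distort the correctly timed lag-1 term

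*Protocol*

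**What the plan says.** Protocol, Specific Aims, Hypothesis 1.1, puts mood first and use second: "Negative mood will predict subsequent same-day cannabis use events". Hypothesis 1.2 in the same section treats mood shortly after use as a response to it: "Negative mood and SI reported within one hour following cannabis use will be lower in intensity".

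Protocol, Statistical Analysis, Data preparation, codes acute use as "1 = self-reported use in the hour preceding the current random prompt, 0 = no use in the last hour". The motive score covers the same window: "whether cannabis was used in the last hour to improve negative mood will be assessed".

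Protocol, Statistical Analysis, Data analysis, Aim 1, then states for Hypothesis 1.1 that "negative affect measures for a) the current random prompt, and b) the prior random prompt (a lag-1 term) will predict" two things. One is "greater cannabis use independent of motivating reason (i.e., lower probability for the zero component of the model"). The other is a higher motive score. The affect measures are "included as predictors for both the zero and non-zero components of the model". For Hypothesis 1.2 the same paragraph expects that "the binary indicator for cannabis use in the last hour will predict lower, less variable scores for the negative affect measures".

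**The concern.** Predictor (a) is mood at prompt t, while the outcome is use, or its motive, in the hour ending at prompt t. The predictor is measured after the outcome window has closed, so an association between them says nothing about mood preceding use. Only predictor (b), mood at prompt t-1, has the order that the Specific Aims require.

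Two consequences follow.

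- **Sign.** For use versus no use, Hypothesis 1.1(a) expects higher same-prompt negative affect with use, and Hypothesis 1.2 expects lower. If cannabis relieves mood, as Aim 1 supposes, that relief pushes the test of 1.1(a) towards refutation.
- **Contamination of (b).** Current mood depends on both earlier mood and recent use. Adjusting for it can link earlier mood to use even when earlier mood has no effect on use, and in the direction that Hypothesis 1.1 predicts.

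Aim 1 asks about a negative-reinforcement cycle. A plan that can reject the antecedent link for one reason and support it for another, neither of them being the link itself, gives results that are hard to interpret.

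**Working it through.** **The plan's own figure.** Table 1 gives power of 99% and 93% for Hypotheses 1.1-1.2 at d = 0.2 and intra-class correlation 0.09. With effective sample size N × m / (1 + (m − 1) × 0.09), two equal groups and an assumed two-sided 5% level:
- 200 × 112 / 10.99 = 2038, power 99.5%.
- 154 × 112 / 10.99 × 0.76 = 1193, power 93.2%.

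Table 1 is reproduced and is not in dispute. High power here also means that a biased coefficient will readily reach significance.

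**Time order.** Setting Data preparation beside Data analysis:

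| Quantity | Time it refers to |
|---|---|
| Mood, predictor (b) | prompt t-1 |
| Use indicator and motive score | the hour ending at prompt t |
| Mood, predictor (a) | prompt t |

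Only (b) comes from an earlier prompt than the one at which use is reported.

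**Size of the distortion.** Let L be mood at t-1, U use in the last hour and C mood at t, with

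C = r × L − d × U + e, var(e) = 1 − r².

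U is independent of L, so there is no antecedent effect. With C and L in one logistic model for U, the slopes are

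- current mood: −d / (1 − r²)
- lag-1 mood: +d × r / (1 − r²).

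Example with d = 0.2, r = 0.5: lag-1 slope 0.2 × 0.5 / 0.75 = 0.133, odds ratio 1.14. With d = 0.44, r = 0.5: 0.293, odds ratio 1.34.

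Simulation of 400,000 prompts with use at 15% of them agrees with this. Odds ratios are per SD of mood; ranges cover repeated runs:

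| Relief d | Autocorrelation r | Current mood alone | Lag-1, joint model | Lag-1 alone |
|---|---|---|---|---|
| 0.2 | 0.3 | 0.81-0.82 | 1.06-1.07 | 1.00 |
| 0.2 | 0.5 | 0.81-0.82 | 1.14 | 1.00 |
| 0.44 | 0.3 | 0.64 | 1.16 | 1.00 |
| 0.44 | 0.5 | 0.64-0.65 | 1.34 | 1.00 |

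**At the trial's size.** A second simulation used 154 participants × 85 prompts, intra-class correlation 0.09, use at about 20% of prompts, adjustment for lag-1 use, participant-clustered standard errors and 300 trials per scenario. At d = 0.2 with no antecedent effect:
- In the joint model the current-mood slope was significantly negative in every trial.
- The false lag-1 odds ratio was 1.08 (r = 0.3) to 1.16 (r = 0.5), significant in 89% to 100% of trials.
- With the current-prompt term removed, rejection in the hypothesised direction was about 1-3%, against a nominal 2.5%.
- With a true lag-1 log-odds of 0.10 per unit of mood, the lag-only model still detected it in 90-92% of trials. The joint model inflated it to 0.17-0.24.

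The logistic model stands in for the use/no-use part of the full zero-inflated beta model.

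**The case against.** The mis-timing of (a) follows directly from the definitions. The objections concern how far the consequences reach, and several of them stand.

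- **A reader might infer that Hypotheses 1.1(a) and 1.2 can never both be confirmed.** The documents do not support that. The Hypothesis 1.2 model includes a lag-1 autocorrelation term, so its use coefficient is conditional on earlier mood. If 1.1(a) is fitted without the lag term, it is a marginal association and may have the other sign. With r = 0.5, d = 0.2 and an antecedent log-odds of 0.7 per SD, the current-mood odds ratio is 1.14 while the Hypothesis 1.2 coefficient is −0.20. A strong antecedent effect is needed: at log-odds 0.1 to 0.3 the current-mood odds ratio stays below 1 (0.86 to 0.95).
- **A reader might infer that lag-1 is biased whenever cannabis relieves mood.** Positive autocorrelation is also required; at r = 0 the lag-1 odds ratio is 1.00. So is joint entry of the two terms. The protocol lists them together as predictors, which makes joint entry the natural reading, but it does not exclude separate models.
- **The relief of 0.2-0.44 SD looks like the exploratory study's range.** The power section gives 0.19 to 0.44 for significant effects but does not say that these are effects of use on mood. It is an assumption here.
- **The sign conflict does not reach the motive score.** Hypothesis 1.2 makes no prediction about motive, so for that outcome the fault is timing alone.
- **Aim 1 is not beyond rescue.** Predictor (b) is already in the plan and, fitted alone, is unbiased in the null simulation. The randomised comparison in Aim 2 is unaffected.

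**Conclusion.** The point holds in this form. Predictor (a) does not test Hypothesis 1.1 as stated, for either the use or the motive outcome. That needs no assumption; it follows from the protocol's own definitions.

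For use versus no use, (a) conflicts with Hypothesis 1.2 unless the antecedent effect is strong and the lag term is left out. With no antecedent effect and relief of 0.2-0.44 SD, the current-mood odds ratio is about 0.81 to 0.64, the wrong side of 1 for Hypothesis 1.1.

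Under joint entry, positive autocorrelation and a mood-lowering effect of use, the lag-1 odds ratio is spuriously about 1.06-1.16 (autocorrelation 0.3) or 1.14-1.34 (0.5). The size of relief, the autocorrelation and the frequency of use are all assumptions, so the ranges show plausible size and do not predict the result. The false-discovery-rate adjustment across the six affect measures offers no protection, because it controls multiplicity and not bias.

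**What to change.** In Data analysis, Aim 1, Hypothesis 1.1:

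- Delete current-prompt negative affect as a predictor, for both the zero and the non-zero part.
- Test only negative affect at the previous prompt of the same day, which is predictor (b) limited to the same-day scope already stated in the Specific Aims.
- Keep same-prompt affect solely as the outcome of Hypothesis 1.2.

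This changes a sentence or two and needs no new data. The cost is that the first prompt of each day has no same-day predecessor: 112 prompts over 14 days is 8 a day, so about 1 in 8 drops out of Hypothesis 1.1. Pairs broken by a missed prompt are lost as well.

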We will conduct a 10-week, multi-method, randomized study, and will recruit 200 school-based adolescents, ages 12-18 years, with daily or near daily cannabis use and current depressive symptoms. The study design is nearly identical to that used in another IRB approved protocol aimed at pilot data collection for the current protocol (#2021P002416), apart from minor modifications to the study population. Participants will complete 2 weeks of real-time EMA during baseline cannabis use (EMA Phase 1; Baseline Use as Usual) to quantify the temporal relationship between cannabis use and mood and SI, and the within- (e.g., concurrent other substance use, social context of use) and between-subject factors (e.g., average severity of cannabis use, depression and SI) that may moderate these linkages. To determine how depression and SI change across short- and longer-term cannabis withdrawal, participants will then be randomized to 8 weeks of monitoring (CB-Mon) or incentivized abstinence via contingency management (CB-Abst). A key aspect of the approach is that the 8-week period is long enough to observe true changes due to cannabis discontinuation, separate from effects of withdrawal and residual cannabinoid exposure that generally subside in 4 weeks. Both groups will complete 1 week of EMA in weeks 1 (EMA Phase 2; Randomized Withdrawal) and 8 (EMA Phase 3; Randomized Sustained Abstinence) of the randomized study period. During all 3 EMA phases, participants will receive 7-9 random, time-stamped prompts per day to ascertain mood and SI in the absence of acute cannabis use, proximal but prior to cannabis use, and during or shortly after cannabis use.

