**Questionnaires:** Surveys will be administered via REDCap, a HIPAA compliant, web-based application hosted by Partners HealthCare designed to support data capture for research studies (http://rc.partners.org/edcredcap), at in-person visits (or virtually via MGB-approved video conference platforms like Microsoft Teams or zoom; V1-12). Construct areas queried include, for example: demographics; cannabis use of family cannabis withdrawal; current and past use of other substance of abuse (e.g., tobacco, alcohol); family rules about substance use; parental messages about substance use; quality of family communication; peer support; social integration; exposure to risky peer networks; self-esteem; coping; depressive, anxiety, and ADHD symptoms; delinquent behaviors; temperament; suicidal ideation; sleeping habits. To enhance reproducibility, measures were drawn from the PhenX Toolkit when available (Hamilton et al., 2011).

**Toxicology:** At all study visits, participants will provide a urine sample, which will be used to qualitatively screen for cannabis use as well as other substances of misuse and quantitatively screen for amount of THC metabolites in urine.

For visits conducted virtually (via MGB-approved video conference platforms like Microsoft Teams or zoom), participants will be given or mailed a qualitative testing and shipping kit. Participants will be guided through the steps of testing the urine sample collected at each visit and will be instructed on how to package the sample for shipment.

**Ecological Momentary Assessment (conducted between V1-V2, V2-V5 and V11-V12):** At baseline, participants will be guided through installing the EMA platform (MetricWire) on their iOS or Android smartphone. Support for app installation and EMA training will be provided throughout the study as needed by phone and via tutorial materials. Participants will be told that surveys will commence the next day and that they should use the app throughout the next 2 weeks in the same way as trained at baseline. During the EMA phases, participants will complete random prompts via MetricWire using a data sampling scheme similar to that used in prior studies (Shiffman et al., 2020). Participants will never be asked to complete >9 random EMA surveys/day. To enhance compliance, participants will be paid a $100 compliance bonus at the end of each EMA phase if ≥80% of random prompts are completed.

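### The lagged mood predictor in Hypothesis 1.1 is set by prompt order, not clock time, so the prior mood can follow the cannabis use it is meant to predict

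*Protocol*

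**What the plan says.** - **Hypothesis.** Specific Aims, Hypothesis 1.1: "Negative mood will predict subsequent same-day cannabis use events". The order is mood first, use later, on the same day.
- **Use variable.** Statistical Analysis, Data preparation: "1 = self-reported use in the hour preceding the current random prompt, 0 = no use in the last hour". The score for use motivated by mood improvement covers the same last hour, with zero meaning no use.
- **Predictors.** Data analysis, Aim 1, Hypothesis 1.1 names two: "negative affect measures for a) the current random prompt", and mood at "the prior random prompt (a lag-1 term"). Both are predictors for the zero and non-zero parts of the model. The lag carries no time condition.
- **Sampling.** General Description of Study Design: "participants will receive 7-9 random, time-stamped prompts per day". The Ecological Momentary Assessment paragraph adds only that prompts are delivered "using a data sampling scheme similar to that used in prior studies". No minimum spacing is given.

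**The concern.** The outcome looks back 60 minutes from the current prompt, while the lag steps back one prompt, however recent. If the prior prompt was 30 minutes ago and the use 45 minutes ago, the lagged mood was recorded 15 minutes after the use. It is then a consequence of use, entered as a cause. The prior prompt also reports the same use, because that use fell within its own preceding hour.

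The lag deserves particular care because the other Hypothesis 1.1 predictor, mood at the current prompt, follows the reported use in every use-positive record. The lag is therefore the only planned predictor that can have the order the hypothesis requires. Contamination of the lag by post-use mood mixes the precipitation effect of Hypothesis 1.1 with the acute effect of Hypothesis 1.2.

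**Working it through.** **Inputs**
- Prompts per day: 7 to 9. The power table uses 112 Phase 1 entries per participant; 112 / 14 days = 8 per day, and 0.76 × 112 = 85, the table's realistic figure. Both reproduce.
- Prompting day: not stated. I assume 15 hours, from the covariate bands "time of day (categorical, 6:00-11:00, 11:00-16:00, 16:00-21:00".
- Spacing rule: not stated. I take three cases: fully random (uniform), one random prompt in each equal block, and a 60-minute minimum gap.

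**How often the order is wrong.** For a gap of g hours below 1, a use spread evenly over the last hour predates the prior prompt with probability 1 − g. The expected share is the integral of P(gap < g) from 0 to 1.

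- Uniform, k prompts in L hours: P(gap < g) = 1 − (1 − g/L)^k.
  - Pairs under 60 minutes: 1 − (14/15)^8 = 0.42.
  - Misordered uses: 1 − (15/9)[1 − (14/15)^9] = 0.23.
- Block, width w = 15/8 = 1.875 h: P(gap < g) = g²/(2w²).
  - Pairs under 60 minutes: 1/(2 × 1.875²) = 0.14.
  - Misordered uses: 1/(6 × 1.875²) = 0.047.
- 60-minute minimum gap: 0 for both.

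Over 7 to 9 prompts, the misordered share is 20% to 25% (uniform) and about 4% to 6% (block). With 76% of 8 prompts answered, simulation gives 19% and 3.7%.

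**What it does to the coefficient.** The simulation has about 0.7 million prompt pairs per case. Its assumptions are:
- mood autocorrelation with a 3-hour time constant;
- 2 uses a day;
- a log hazard ratio of 0.2 per SD of negative mood;
- an acute effect of use that decays over 2 hours;
- 76% completion.

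Acute effects of 0.2 and 0.44 SD correspond to the protocol's planning effect and the top of its preliminary range (0.19 to 0.44). The table gives the log odds ratio for use in the last hour, with the lag entered alone (standard error about 0.004).

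| Acute effect of use | Prompts | Prior prompt | Last prompt ≥60 min earlier |
|---|---|---|---|
| Relief 0.44 SD | uniform | 0.086 | 0.109 |
| Relief 0.44 SD | block | 0.109 | 0.111 |
| Relief 0.2 SD | uniform | 0.112 | 0.110 |
| Relief 0.2 SD | block | 0.127 | 0.124 |
| Worsening 0.2 SD | uniform | 0.153 | 0.103 |
| Worsening 0.2 SD | block | 0.136 | 0.121 |

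The largest attenuation is 1 − 0.086/0.109 = 21%. In the worsening rows the inflation is 0.153/0.103 − 1 = 49% (uniform) and 0.136/0.121 − 1 = 12% (block).

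With no true precipitation, uniform prompts and 0.44 SD relief, the lag log odds ratio was −0.04 to −0.07, depending on the simulation set-up. It was close to zero under the 60-minute rule.

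**Current-prompt mood in the same model.** Under the same null and 0.44 SD relief, entering current-prompt mood alongside the lag pushes the lag coefficient to about +0.15, even after re-pairing at 60 minutes. Re-pairing alone is therefore not enough.

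**The case against.** The strongest reply is that the protocol is silent on spacing, not wrong. Spacing may be set in the app, follow from the cited sampling scheme, or appear in an analysis plan that is not shown. With a 60-minute gap the problem vanishes, and with block prompts it is small. This limits the size of the point. It does not remove it, because the lag rule itself is stated, is indexed by prompt order, and does not secure the order the hypothesis asserts. Hypothesis 1.2, in Specific Aims, does set a one-hour condition for its comparison prompts.

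A second reply is that the lag-1 autocorrelation term may absorb the fault, since a misordered use is also reported at the prior prompt. In a simulation with uniform prompts and 0.44 SD relief, adding prior use moved the lag log odds ratio from 0.076 to 0.104, against 0.110 with the time-based lag. Most of the bias goes. However, the protocol does not say whether that term enters the probability of zeros, which is where use versus non-use is modelled.

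Three stronger readings are tempting but not supported:
- **The bias always hides precipitation.** Its direction depends on whether use relieves or worsens mood, and at 0.2 SD relief with precipitation present it was not visible.
- **42% of pairs are wrong.** That is the share of pairs under 60 minutes. Many are correctly ordered; the relevant figure is 23% of last-hour uses.
- **Hypothesis 1.2 is over-adjusted by the same lag.** The quoted lag belongs to Hypothesis 1.1, and the general model's lag-1 term may be a residual autocorrelation. Even as a lagged outcome it did not shrink the relief estimate (−0.167 against −0.166 uniform; −0.178 against −0.174 block, at 0.44 SD).

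**Conclusion.** The point holds for Hypothesis 1.1. As written, the lagged mood can follow the use it should predict, contrary to the hypothesis. The affected share of last-hour uses is about 23% with fully random prompts, about 5% with block prompts and 0% with an enforced 60-minute gap, given 8 prompts in an assumed 15-hour day. The bias is downward if use relieves mood and upward if use worsens it. It is material mainly with fully random prompts and generally small with block prompts. The shares follow from geometry and the stated assumptions. The coefficients rest on assumed mood dynamics and a simple logistic model, so they show direction and order of size only.

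**What to change.** Define the Hypothesis 1.1 lagged predictor as mood at the last completed prompt on the same day at least 60 minutes before the current prompt, so that it precedes the whole use window. Base the precipitation test on this predictor without current-prompt mood in the same model, and report current-prompt mood only as a concurrent or post-use association. State the prompt-spacing rule; if the app already enforces 60 minutes, saying so settles the ordering of the lag.

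The change is to analysis wording only, since prompts are already time-stamped and collected data can be re-paired. The cost is that some correctly ordered short-gap pairs are re-paired with an older mood report or dropped. That loses some of the mood reports closest to use, which the design set out to capture. Changing the app's spacing during the trial is not part of this fix, because it would give earlier and later participants different Phase 1 sampling.
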